#### Fourth objective

Individual characteristics predicting the program success at the individual level are obtained in secondary schools:Personality traits assessed by the Level of Personality Functioning Scale—Brief Form (LPFS-BF; [36])Internal self-blame assessed by the Attributions for Victimization Experiences Measure [37, 38]Callous-unemotional traits within the last 6 months assessed by the Inventory of Callous-Unemotional Traits—Youth Version (ICU; [39])

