### Sample size {14}

To estimate the required sample size, Monte Carlo simulations were carried out using Stata 16.1 with the following assumptions: Two measurement points of 15 secondary schools per group with 10 classes per school and 5 primary schools per group with 4 classes per school are expected to take part in the study. In each class, 25 pupils are expected. Baseline bullying prevalence is estimated to be 15%, and the intervention is expected to lead to a relative reduction in bullying of 25%. The standard deviation (*SD*) of bullying rates between schools is *SD* = 0.2 on the logit scale; the *SD* of classes within schools is *SD* = 0.4 on the logit scale. This leads to an intraclass correlation coefficient on the school level of 0.011 and 0.057 on the class level. The assumptions were chosen so that the simulated data corresponded to the data from the OBPP study [18]. With these assumptions, 1000 data sets were simulated and analysed by three-level mixed logistic regression with group, measurement point, and their interaction as fixed effects and random intercepts on the school (level 3) and class (level 2) level. Using an alpha-error probability of 0.05, with 40 schools and 8500 pupils (4250 IG and 4250 CG) the power would be 86%.

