## Data collection and management

### Plans for assessment and collection of outcomes {18a}

Pupils complete anonymous online self-report questionnaires created with LimeSurvey. The responsible teachers read standardized instructions to their pupils and every pupil receives a randomly assigned Login ID (random combination of numbers and letters) for registering on the start page of the survey. In the beginning of the survey, all pupils decide about their participation in the accompanying evaluation study. Approving pupils are asked to create an individual code to enable the association of repeated assessments to the same pupil and receive additional questions during the course of the survey. The assessments take place at school during regular class times and the duration is a maximum of 90 min. The first secondary schools conducted their baseline in March 2022. The first primary schools conducted their baseline in October 2023.

The following scales are used in primary as well as secondary schools:Demographics (2 items)Bullying Screening ( [28, 29]; 6 items)Bullying circumstances for victims, perpetrators, and bystanders based on the Olweus Bullying Questionnaire Revised (OBQ-R; [41]; maximum of 18 items for primary schools and maximum of 25 items for secondary schools, exact number depends on given answers in the Bullying Screening)KIDSCREEN-10 ( [30]; 10 items) for primary schools or KIDSCREEN-27 ( [31]; 27 items) for secondary schools:oKIDCREEN-10: Cronbach’s alpha = 0.82, test–retest reliability assessed by an intraclass correlation coefficient (*ICC*) = 0.70, and demonstrated validity [30]oKIDSCREEN-27: Test–retest reliability *ICC*s = 0.61–0.74 for the different dimensions and was found to be valid [31]

In secondary schools, the following scales are additionally used:Strengths and Difficulties Questionnaire (SDQ; [32]; 25 items): Mean Cronbach’s alpha = 0.73 and mean test–retest reliability after 4 to 6 months = 0.62Self-harming behaviour within the last 12 and 3 months based on the Self-Injurious Thoughts and Behaviours Interview (SITBI; [33]; 6 items)Internet Gaming Disorder Scale (IGDS; [34]; 11 items): Reliability coefficients of 0.82 and 0.83 [42]Social Media Disorder Scale (SMDS; [35]; 11 items): Reliability coefficient of 0.57Level of Personality Functioning Scale—Brief Form (LPFS-BF; [36]; 12 items): Cronbach’s alpha = 0.82 and promising construct validity

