## Statistical methods

### Statistical methods for primary and secondary outcomes {20a}

For the primary outcome (i.e. reduction in victimization and perpetration rates in IG compared to CG; see first objective), three-level mixed effect regressions with the dependent variables bullying victims (yes/no) and perpetrators (yes/no) will be conducted. For secondary outcomes (i.e. reduction in psychological distress, self-harming behaviour, and problematic Internet use in IG compared to CG; see second objective), dependent variables will be scores of the KIDSCREEN-27, SDQ, self-harming behaviour, IGDS, and SMDS (grades 5 to 9) or the scores of the KIDSCREEN-10 (grades 3 and 4). The fixed effects are the factors group (IG, CG), measurement point (T0, T1, T2), and the interaction of both (group × measurement point). The hierarchical random effects are the factors school (level 3) and class (level 2). The analyses are conducted using Wald tests (interaction group × measurement point). In order to investigate the third objective (i.e. effectiveness of specific program components), a variable reflecting the implementation of a specific component of the program (assessed via teacher surveys as well as via eLearning utilization) is included as a covariate and as an interaction term with group, measurement point, and their triple interaction in the model. The triple interaction allows for the identification of the effectiveness of a specific program component. The analysis is repeated for different components. The fourth objective (i.e. individual characteristics predicting program success at the individual level) is investigated by adding a pupil level to the multilevel analysis. The association of surveys from different time points to pupils is ensured by individual codes. Codes with a Levenshtein distance not greater than 2 are assigned to the same pupil. For each individual characteristic (i.e. personality traits, internal self-blame, callous-unemotional traits), the model of objective one is extended by the characteristics at baseline as a predictor and a pupil specific random intercept. In order to compensate for the small number of randomized schools, we will apply a small sample error correction to each analysis using school-level bootstrap. All calculations are performed with a significance level of 0.05.

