### Methods in analysis to handle protocol non-adherence and any statistical methods to handle missing data {20c}

The analysis is an intention to treat analysis; whole schools were randomly assigned to the two conditions intervention group vs. control group. In order to enable sub-analyses differentiated by program dose, a score based on the intensity of the central program components will be created for each school.

Sensitivity analyses are done on the complete-case sample, i.e. excluding schools where measurement points are missing.

To deal with our fourth objective (individual characteristics predicting the program success at the individual level), the association of questionnaires from different time points to pupils is required. Therefore, individual codes with a Levenshtein distance not greater than 2 are assigned to the same pupil. Apart from this strategy to reduce missings, no missing data is imputed.

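### Linking pupils by code distance 2 alone does not define a unique set of pupils and, depending on the unstated code format, can join different children in the exploratory fourth objective

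*Protocol article*

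**What the plan says.** All references are to the protocol article. Under Plans for assessment and collection of outcomes {18a}: "Approving pupils are asked to create an individual code to enable the association of repeated assessments to the same pupil". The length, alphabet and construction of the code are not given.

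Statistical methods {20a} says that "The association of surveys from different time points to pupils is ensured by individual codes" and then gives the rule: "Codes with a Levenshtein distance not greater than 2 are assigned to the same pupil". The section on non-adherence and missing data {20c} repeats it ("individual codes with a Levenshtein distance not greater than 2 are assigned to the same pupil"), ties it to the fourth objective, and says that apart from this step nothing is imputed.

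The fourth objective "is investigated by adding a pupil level to the multilevel analysis", with the baseline characteristic as predictor and a random intercept per pupil. Under Outcomes {12}, Fourth objective: "Individual characteristics predicting the program success at the individual level are obtained in secondary schools". Objectives {7} describes the third and fourth objectives as exploratory.

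**The concern.** Both statements are assignment rules with the distance threshold as their only condition. Neither mentions a common school, different waves, a unique match, or what to do when one code lies near several others.

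A false link pairs one child's baseline trait with another child's follow-up answer. If linkage errors are unrelated to the traits, this weakens the trait associations that the fourth objective looks for and distorts the variance of the pupil intercept. The planned sensitivity analysis would not reveal it: it drops schools with missing time points and leaves the linkage unchanged.

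**Working it through.** **The plan's own figures.** The article gives no figure for the linkage rule. Its sample-size figures reproduce and do not involve linkage:

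- N = 2 × (15×10×25 + 5×4×25) = 8,500.
- School ICC = 0.04/(0.04 + 0.16 + π²/3) = 0.0115. Class ICC = 0.20/(0.20 + π²/3) = 0.0573.
- Power: the log odds ratio for 15% against 11.25% is 0.331. There are 170 classes of 25 per arm and time point. With the class effect (variance 0.16) drawn anew at each time point, the variance is [3 × (1/(25×0.15×0.85) + 0.16) + (1/(25×0.1125×0.8875) + 0.16)]/170 = 0.01166. The SE is 0.108 and the two-sided power at 0.05 is 86.5%, against 86% stated. With the class effect shared over time it would be 96.1%.

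**Logic of the rule.** Take three invented codes: ABCD, ABEF and GHEF. The first and second differ by 2, and so do the second and third, but the first and third differ by 4. The rule makes the second code the same pupil as each of the others, yet gives no ground for treating those two as one pupil. Two analysts could form different pupils from the same data. This holds whatever the usual code length; only its frequency depends on the format.

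**Frequency.** Inputs: secondary schools only, 2×15×10×25 = 7,500 planned pupils, so 7,499 others in the whole secondary sample, 249 in a school of 250 and 24 in a class of 25. Code formats are assumptions. Uneven letters have frequency proportional to rank^−0.8 over 26 letters; day of month is uniform on 1–30.

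Expected false candidates = (number of other pupils) × P(distance ≤ 2 between two different pupils' codes). P comes from 1,000,000 simulated pairs per format. For random codes of length L over a characters it is checked against the substitution-only formula Σ(k=0..2) C(L,k)(a−1)^k / a^L, which leaves out insert–delete pairs and so runs slightly low:

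- 4 letters: (1 + 4×25 + 6×625)/26⁴ = 3,851/456,976 = 0.0084 (simulated 0.0088).
- 6 letters: (1 + 6×25 + 15×625)/26⁶ = 9,526/308,915,776 = 3.1×10⁻⁵ (simulated 3.8×10⁻⁵).
- 8 letters/digits: (1 + 8×35 + 28×1,225)/36⁸ = 1.2×10⁻⁸ (no hits in the simulation, so the formula is used).

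| Assumed format | P(distance ≤ 2) | Whole secondary sample | One school | One class |
|---|---|---|---|---|
| 3 uneven letters + day | 0.0133 | 99 | 3.3 | 0.32 |
| 4 random letters | 0.0088 | 66 | 2.2 | 0.21 |
| 4 uneven letters + day | 0.00162 | 12 | 0.40 | 0.04 |
| 6 random digits | 0.00149 | 11 | 0.37 | 0.04 |
| 4 uneven letters + day + month | 0.000202 | 1.5 | 0.05 | 0.005 |
| 6 random letters | 3.1–3.8×10⁻⁵ | about 0.25 | 0.01 | 0.001 |
| 8 random letters/digits | 1.2×10⁻⁸ | 0.0001 | negligible | negligible |

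The gain from a school limit is the ratio of pool sizes, 7,499/249 ≈ 30; for a class limit it is 7,499/24 ≈ 312. Recruitment {15} reports 27 secondary schools. At 250 pupils each that is 6,750, which lowers the whole-sample column by about a tenth. Pupils who decline the study make no code and lower it further.

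**The case against.** The strongest objection is that this argues from silence. A journal article may leave code format, matching order and tie handling to a fuller document, and one may exist. That holds for the code format, whose absence is not the point here. It does not remove the fault in the rule itself: the article gives the criterion twice, as an assignment and without qualification, and calls the linkage ensured. As stated, it does not determine the pupils.

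Four stronger readings are tempting, and the document does not support them.

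- **Pupils are merged across the whole trial.** The pupil level is added to a hierarchy of classes within schools, and a link between schools would break that nesting. Matching within school is the more plausible intention, so the within-school column is the fairer guide. It does not settle ties inside a school.
- **The codes are short, so many children are merged.** The article says that pupils create the code, not that it is short. With random codes of six or more letters/digits, false candidates are rare even across the full sample.
- **Trait associations shrink by a known amount.** The table counts near codes, not false links. A pupil with an exact match can have several near neighbours and still be linked correctly. No false-link share can be derived.
- **The trial's main result is at risk.** The primary and secondary models have school and class levels but no pupil level, and {20c} ties the linkage to the fourth objective.

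**Conclusion.** The point holds in a limited form. The linkage rule is not one-to-one or transitive, so it does not yield a unique set of pupils, and it can join different children. Within a school, the expected number of false candidates per pupil is about 2–3 for the two shortest formats assumed, about 0.4 for 4 uneven letters plus day, and 0.01 or less for random codes of six or more letters. These figures rest on assumed formats and on the planned 250 pupils per secondary school. The direction of harm is probably towards weaker trait associations; its size is unknown. Because only an exploratory objective depends on the linkage, severity is low.

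**What to change.** State the code format, and replace the single threshold with an ordered rule:

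1. Link exact codes first.
2. Among the rest, accept a distance of 2 or less only between different waves within the same school, and only if each code is the other's unique nearest.
3. Use grade and gender to break ties or to flag implausible links, not as mandatory exclusions, because a pupil may repeat a grade or mis-enter gender. Leave ties that remain unlinked.
4. Report link rates by arm, and repeat the fourth-objective analysis on exact matches only.

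No new data are needed: school and class are already levels of the model, and gender and grade group are already planned subgroups in {20b}. The cost is a few lines of linkage code, one extra sensitivity run and somewhat fewer linked pupils, including any who move between trial schools.

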## Objectives {7}

The primary aim of this CRT is to evaluate the effectiveness of the newly developed school-based blended-intervention bullying prevention program *Bullying&You*. We aim to investigate whether *Bullying&You* leads to a reduction in victimization and perpetration rates among pupils in the intervention group (IG) compared to a waiting control group (CG) within 1 year (T1) and 2 years (T2), respectively (primary objective). Secondary aims are to explore whether the program leads to a reduction in psychological distress, self-harming behaviour, and problematic Internet use in the IG compared to the CG (second objective). In addition, exploratory analyses will aim to evaluate which specific components of the program are particularly effective in reducing bullying (third objective), and which characteristics of pupils predict program success at the individual level (fourth objective).

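### The model for the fourth objective has no interaction between the pupil characteristic and group × measurement point, so it cannot show which pupils the program works for

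*Protocol article*

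**What the plan says.** All references are to the protocol article.

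- **Target.** Objectives {7} lists, among the exploratory analyses, "which characteristics of pupils predict program success at the individual level (fourth objective"). The Fourth objective paragraph under Outcomes {12} names personality functioning, internal self-blame and callous-unemotional traits: "Individual characteristics predicting the program success at the individual level are obtained in secondary schools".
- **Program effect.** Statistical methods {20a} sets out the objective-one model: "The fixed effects are the factors group (IG, CG), measurement point (T0, T1, T2), and the interaction of both (group × measurement point"), with school and class as random effects. The test is also named: "The analyses are conducted using Wald tests (interaction group × measurement point").
- **Third objective.** In the same section, the variable for a program component "is included as a covariate and as an interaction term with group, measurement point, and their triple interaction in the model". The reason is given: "The triple interaction allows for the identification of the effectiveness of a specific program component".
- **Fourth objective.** A few sentences later, for each characteristic, "the model of objective one is extended by the characteristics at baseline as a predictor and a pupil specific random intercept".

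The section on additional analyses {20b} plans subgroups by gender, school type and grade group, and looks at school size and baseline victimization. It does not mention the three traits. The section on non-adherence and missing data {20c} covers only the linking of questionnaires for this objective.

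**The concern.** The plan measures program success as the difference between arms in the change over time. A characteristic predicts that success only if the difference varies with the characteristic. The objective-four model adds one fixed effect for the trait and one random intercept for the pupil. Neither lets the program effect vary with the trait.

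The model will still return a trait coefficient, and for traits such as callous-unemotionality or self-blame it may well be large. That coefficient describes risk of being a victim or perpetrator. Read against the stated objective, it could be taken for evidence on who benefits. The article's Discussion says that moderators of preventive programs have scarcely been researched, so an error here would fall on a question the trial particularly wants to inform.

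**Working it through.** **The plan's own figure.** No figure is given for the fourth objective. The only computed power, 86% in Sample size {14}, is for group × measurement point, and the inputs used below come from that section. Per arm there are 15×10×25 + 5×4×25 = 4250 pupils in 15×10 + 5×4 = 170 classes. Rates are 15% and 0.75×15% = 11.25%, a log odds ratio of 0.331 in absolute value. The plan states "Using an alpha-error probability of 0.05" without sidedness; two-sided is assumed. If class effects are redrawn at each wave (the text does not say), the variance is

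3/(4250×0.15×0.85) + 1/(4250×0.1125×0.8875) + 4×0.16/170 = 0.00554 + 0.00236 + 0.00376 = 0.01166,

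so SE = 0.108 and power = Φ(0.331/0.108 − 1.96) = 86.5%. The figure reproduces and is not in dispute. It says nothing about the trait analysis.

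**What the stated model can estimate.** Let G be the arm, T1 and T2 the wave indicators, X the baseline trait, and u the school, class and pupil intercepts. As written:

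logit P = β0 + βG·G + β1·T1 + β2·T2 + βG1·G·T1 + βG2·G·T2 + γX + u

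The program effect at T1 for a pupil with trait value X is

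[η(G=1,T1) − η(G=1,T0)] − [η(G=0,T1) − η(G=0,T0)] = βG1.

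γX cancels within each bracket, as does the pupil intercept. The effect is βG1 at every X. With the third objective's structure applied to X, the same difference is βG1 + δ1·X, and δ1 (characteristic × group × T1) is the quantity the objective asks for.

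**Illustrative simulation.** The trait effects below are assumptions and are not in the documents. The set-up was 30 secondary schools × 10 classes × 25 pupils = 7500 pupils, waves T0 and T1, baseline rate 15%, program log odds ratio −0.331, school SD 0.2, class SD 0.4, a standard normal trait and 200 data sets per row. Both models were fitted by logistic regression with school-clustered standard errors, which simplifies the planned mixed model. Effects are log odds ratios per SD of the trait.

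| Assumed trait effect | Coefficient, model as written | Significant | Triple-interaction coefficient | Significant |
|---|---|---|---|---|
| Risk 0.4, modification 0 | 0.390 | 100% | 0.004 | 7% |
| Risk 0.4, modification 0.3 | 0.448 | 100% | 0.289 | 87% |
| Risk −0.075, modification 0.3 | −0.016 | 8.5% | 0.310 | 95.5% |

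With 200 data sets, the 7% has a Monte Carlo standard error of √(0.07×0.93/200) = 1.8 points, so it is compatible with 5%.

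**Why row 2 differs from row 1.** Modification acts in one of four arm-by-wave cells. Weighting cells by p(1−p), that cell carries about 0.0998/(3×0.1275 + 0.0998) = 0.207 of the information, so about 0.3×0.207 = 0.06 enters the pooled coefficient. This agrees with 0.448 − 0.390 = 0.058. Some modification therefore does reach the trait coefficient, but 0.448 from a modifier looks the same as 0.448 from a slightly stronger pure risk factor.

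**The case against.** **The article is condensed, and calling the trait a predictor may be shorthand for a model with interactions.** This is possible; the plan to study how baseline victimization influences effectiveness shows that the authors think about effect modification. But the article states the objective-four model rather than leaving it open, and a few sentences earlier it spells out the interactions for the third objective and why they are needed. An analyst following the text would fit a model without them. If interactions were intended, the sentence still needs correcting.

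**The objective is exploratory.** This stands and limits the severity.

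**A common odds ratio gives different absolute reductions at different baseline risks, so a risk factor does predict benefit in that sense.** True, but this follows from the logit scale alone. The model assumes it and does not test it.

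**Stronger readings that a reader might infer.**
- *The trait coefficient carries no information about modification, or is the same with or without a program.* The arithmetic above shows otherwise: modification leaks in. The fault is that it cannot be separated from risk.
- *A pure risk factor would almost certainly be declared a predictor of success.* That depends on a trait–bullying association that the documents do not give. It also depends on the number of consenting, linkable pupils. Under {18a}, only consenting pupils create the linking code and answer the self-blame and callous-unemotional scales, and no rates are stated.
- *Main-effect p-values will be reported as predictors of response.* The article does not say which coefficient is tested for this objective. The only test it names is the one on group × measurement point.

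**Conclusion.** Wrong as written, at moderate severity. The stated model holds the program effect constant on the logit scale across trait values and cannot distinguish a risk factor from an effect modifier, so the fourth objective is not answered. This follows from the model's algebra and needs no assumption about effect sizes.

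The simulation percentages are illustrations only. They rest on assumed trait effects, on all 7500 planned secondary pupils being linked at two waves (Recruitment {15} reports 27 of the 30 secondary schools), and on a simplified fit. They show that the model can err in both directions, not how often it would in this trial. The primary and secondary analyses, the sample size and the 86% power are untouched.

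**What to change.** For each characteristic, extend the objective-one model by the characteristic, characteristic × group, characteristic × measurement point and characteristic × group × measurement point. Keep the pupil random intercept, and test the triple interaction.

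The model has three waves, so name the T1 component as the main contrast and report T2 separately. The waiting controls start the program after one year ({6b}), so at T2 the arms differ in length of exposure rather than in having the program or not.

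Report the estimated program effect at low and high trait values with confidence intervals, and label the trait main effect a risk-factor result.

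The change needs no new data: baseline characteristics and linkage by individual code are already planned. The cost is a few lines of specification and less precise estimates, since an interaction is estimated less precisely than a main effect and only linked pupils contribute. That is acceptable for an exploratory objective, provided that a non-significant interaction is not read as proof that the program works equally for all pupils.
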